### Data management, collection and monitoring

All protocol-required information collected during the study will be entered by the investigator in the electronic case report forms (CRF). The investigator should complete the CRF as soon as possible after information is collected. An explanation should be given for all missing data. The completed CRF will be reviewed and signed by the investigator. The main investigator will continuously monitor data. Data will be stored in the secured network of Sun Yat-sen University and for security reasons, in an external hard drive which will be used to back up regularly the database.

### Statistical methods

For statistical analysis of the quantitative variables with normal distribution, the mean, standard deviation (SD), median and interquartile range will be calculated. Group comparisons will be made using t tests or Mann-Whitney U test for continuous variables. Associations between the categorical variables will be tested with the Chi-Square-test or the Fisher exact test, when appropriate. Paired values (before and after therapies) will be compared for each patient using a paired t test or a Wilcoxon test. The data will be analyzed using IBM SPSS Statistics for Windows, version 27.0 (IBM Corporation, Armonk, NY, USA). A significance threshold of p < 0.05 will be adopted for all tests.

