## Abstract

**Background:**

Neoadjuvant chemoradiotherapy (NCRT) and total mesorectal excision are standard treatment regimen for patients with locally advanced rectal cancer (LARC). This sphincter-saving treatment strategy may be accompanied by a series of anorectal functional disorders. Yet, prospective studies that dynamically evaluating the respective roles of radiotherapy, chemotherapy and surgery on anorectal function are lacking.

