#### Outcomes

Evaluations will take place at baseline (T1), after radiotherapy or chemotherapy (before surgery, T2), after surgery (before closing the temporary stoma, T3), and at follow-up visits (every 3 to 6 months, T4, T5……). Follow-up for each patient will be at least 2 years.

The primary outcome is the average resting pressure (ARP) of anal sphincter. The secondary outcomes are maximum anal sphincter contraction pressure, Wexner continence score and LARS score. We will use high-resolution anorectal manometry (Solar GI HRM; MMS, Enschede, the Netherlands) to assess the average resting pressure and maximal contraction pressure, which has proven to be adequate for clinical use [23, 24]. This test will be performed by the trained physicians. In addition, we will use Wexner continence score and LARS score to assess fecal incontinence symptoms of patients following sphincter-preserving rectal cancer surgery.

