### Allocation

The study is a prospective, observational, controlled study without randomization. Treatment decisions will be made by multidisciplinary team for eligible patients who voluntarily sign the consent form. All patients will receive evaluation of the anorectal function through anorectal manometry, Wexner continence score and LARS score before and after therapies and at follow-up visits.

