There are some limitations in this study. The study design is observational but not randomized and blinded. At the end of the study, we will stratify the patients according to age, sex, and cancer stage. After completing the recruitment and preliminary evaluation, we will further determine whether to enlarge the sample size or not.

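### Treatment is chosen by clinicians, but the stated between-group tests of anal resting pressure are unadjusted and make no stated use of the baseline value

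*Protocol article*

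**What the plan says.** The Allocation section of the protocol article is explicit about the design: "The study is a prospective, observational, controlled study without randomization". It adds: "Treatment decisions will be made by multidisciplinary team for eligible patients who voluntarily sign the consent form". Under Interventions, the choice among NCRT plus surgery, NCT plus surgery and surgery alone follows treatment guidelines. The abstract's Background calls NCRT with total mesorectal excision the standard regimen for this disease.

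The Objectives and Discussion set a comparative aim: to separate the roles of the three strategies in anorectal function. Under Outcomes: "The primary outcome is the average resting pressure (ARP) of anal sphincter". ARP is measured at baseline (T1) and at each later stage.

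The Statistical methods section gives the between-group method: "Group comparisons will be made using t tests or Mann-Whitney U test for continuous variables". Baseline values appear only in a within-patient comparison: "Paired values (before and after therapies) will be compared for each patient using a paired t test or a Wilcoxon test". No regression, baseline adjustment, matching or weighting is named.

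The limitations paragraph of the Discussion acknowledges that the study is neither randomised nor blinded, and continues: "At the end of the study, we will stratify the patients according to age, sex, and cancer stage".

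**The concern.** If one regimen is standard, patients who receive another were probably selected for a reason, such as stage, age, fitness or tumour features. Some of those reasons may also bear on sphincter pressure. A two-sample t or Mann-Whitney test credits any such pre-existing difference to the treatment, although the study's purpose is to attribute differences in function to radiotherapy, chemotherapy or surgery.

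The best single safeguard, each patient's own ARP before treatment, is already planned at T1. The paired tests use it to describe change within patients, but they do not adjust a difference between groups. More patients do not help either: a larger sample shrinks the standard error and leaves the bias where it was.

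**Working it through.** **Inputs from the Sample size section.** ARP 32.7 (SD 17) versus 45.3 (SD 18) mmHg, so a difference of 12.6; power 80%; alpha 0.05; ratio 1:1; 122 per group before losses. Pooled SD = √((17² + 18²)/2) = 17.5.

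**Assumptions, not in the documents.** Two-sided testing; no true treatment effect when false-positive rates are computed; an imbalance *b* of 2, 3 or 4 mmHg; a correlation *r* of 0.5 to 0.7 between T1 and later ARP.

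**1. The plan's own figure.** n = 2 × (1.96 + 0.84)² × 17.5² / 12.6² = 30.3, so 31 per group, not 122. The 122 is obtained if the difference is halved to 6.3 mmHg, which the document does not say. That is a separate matter. Here 122 serves only as the planned group size, and the present point does not depend on how it was reached.

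**2. Standard error of an unadjusted difference.** SE = 17.5 × √(2/122) = 2.24 mmHg.

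**3. False-positive rate under bias.** P(|Z + bias/2.24| > 1.96). If the imbalance acts in full on the outcome, bias = *b*. If it is an imbalance in T1 ARP, only *r* × *b* carries through to follow-up.

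| *b* (mmHg) | Bias in the outcome = *b* | T1 imbalance, *r* = 0.5 (bias) | T1 imbalance, *r* = 0.7 (bias) |
|---|---|---|---|
| 2 | 15% | 7% (1.0) | 10% (1.4) |
| 3 | 27% | 10% (1.5) | 16% (2.1) |
| 4 | 43% | 15% (2.0) | 24% (2.8) |

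**4. Check by simulation.** For T1 imbalances of 0.2, 0.3 and 0.5 SD (3.5, 5.3 and 8.8 mmHg) with *r* = 0.5, the formula gives 12%, 22% and 50%. Simulating 122 per group gave 12.5%, 21.7% and 49.7% for the t test, and 5.0%, 4.7% and 4.7% for ANCOVA on T1 ARP. ANCOVA holds its level here because T1 ARP is the only confounder in the simulation.

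**5. Effect of sample size.** With a 3 mmHg bias in the outcome, the rate is 16% at 61 per group, 27% at 122 and 47% at 244. The possible enlargement mentioned in the limitations would not help.

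**6. Precision gained.** The detectable difference at 122 per group is (1.96 + 0.84) × 2.24 = 6.3 mmHg. Adjusting for T1 ARP multiplies it by √(1 − *r*²): 5.4 mmHg at *r* = 0.5 and 4.5 mmHg at *r* = 0.7.

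**The case against.** The strongest reply is that the authors know the limitation, say so, and promise to stratify by age, sex and stage. They may also hold a fuller analysis plan. This stands in part. Three plausible confounders are named, and a stratified analysis pooled over strata would adjust for them. But the sentence is not tied to the ARP comparison or to any test, and it leaves out T1 ARP and centre. Nor is this a detail left to another document: the article states a between-group method, and that method does not fit the design.

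Four stronger readings are tempting, and the documents do not support them.

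- *The comparison is confounded.* No baseline data by group are given, and nothing says sphincter pressure influences the team's choice. It is open to confounding, no more.
- *Baseline is ignored.* The paired tests use T1. The group-comparison sentence also does not say whether raw values or changes are compared. What can be said is that no baseline adjustment between groups is stated.
- *Stratification leaves cells too small to use.* Crossing three two-level factors would leave 122/8, about 15 per group per cell, with a detectable difference of about 18 mmHg in a single cell. The article gives no number of levels and does not say the factors are crossed or the cells tested singly. Pooling over balanced strata keeps about 6.3 mmHg, and one two-level factor at a time leaves 61 per group and 8.9 mmHg.
- *Stage will be taken after neoadjuvant treatment.* The text does not say which stage is meant. This calls for a clarification and is not a demonstrated error.

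**Conclusion.** The point holds in this form. Treatment is chosen rather than randomised, the only stated between-group method for continuous outcomes is unadjusted, and the stratification in the limitations does not cure this. As written, the primary comparison cannot separate a treatment effect on ARP from differences present before treatment.

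That conclusion rests on the text alone. Its size does not: the false-positive rates of 15% to 43% assume 2 to 4 mmHg of bias in the outcome, and the lower range of 7% to 24% assumes an imbalance of that size in T1 ARP with a correlation of 0.5 to 0.7. Neither the imbalance nor the correlation can be derived from the documents, so these figures show sensitivity and are not a forecast.

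**What to change.** In Statistical methods, make the primary between-group comparison of ARP a regression (ANCOVA) on treatment group, adjusted for T1 ARP, age, sex, clinical stage before treatment, and centre. For the secondary outcomes use the analogous baseline-adjusted model, with a form suited to bounded scores for Wexner (0–20) and LARS (0–42). Keep the t and Mann-Whitney tests as descriptive. Say how the stratification by age, sex and stage relates to this model, and which stage is meant. State that unmeasured confounding remains. Propensity weighting is an optional sensitivity analysis.

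The cost is protocol wording and some analyst time. ARP is already measured at T1; age, sex and TNM stage are listed in Table 1; and centre is known, since two hospitals recruit. The timing of the stage record should be confirmed. Recruitment is expected to run to the end of December 2026, so the model can be fixed before results are seen. The downside is that the result then depends on a regression model, which removes only measured confounding.

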### Objectives

This prospective, observational, controlled, multicentre study aims to dynamically evaluate the different roles of NCRT with surgery, neoadjuvant chemotherapy (NCT) with surgery and surgery only on the anorectal function of patients with LARC by using anorectal manometry, Wexner continence score and LARS score. In addition, the correlation between manometric findings and Wexner continence score or LARS score after different treatment regimens would be investigated.

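### Change in resting pressure is tested only within patients, and group tests have no stated visit or scale, so no stated analysis compares change between the three non-randomised strategies

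*Protocol article*

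**What the plan says.** All of this is in the protocol article.

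- **Aim (Objectives).** In locally advanced rectal cancer, the project "aims to dynamically evaluate the different roles of NCRT with surgery, neoadjuvant chemotherapy (NCT) with surgery and surgery only on the anorectal function".
- **Outcome and visits (Outcomes).** "The primary outcome is the average resting pressure (ARP) of anal sphincter". No visit is named and no change from baseline is mentioned. Measurements are at baseline (T1), after neoadjuvant treatment and before surgery (T2), after surgery and before stoma closure (T3), and then every 3 to 6 months. "Follow-up for each patient will be at least 2 years".
- **Analysis (Statistical methods).** For groups: "Group comparisons will be made using t tests or Mann-Whitney U test for continuous variables". For change: "Paired values (before and after therapies) will be compared for each patient using a paired t test or a Wilcoxon test". For all of them: "A significance threshold of p < 0.05 will be adopted for all tests".
- **Allocation.** Treatment is not randomised; a multidisciplinary team decides.
- **Sample size.** The basis is a difference in resting pressure levels between two groups at ileostomy closure, 32.7 (SD 17) against 45.3 (SD 18) mmHg.
- **Discussion, limitations.** Patients will be stratified by age, sex and cancer stage at the end of the study. Baseline ARP is not in that list, and Statistical methods does not mention the stratification.

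**The concern.** The aim is a contrast between strategies in how function changes. The plan gives each purpose its own method, and the method given to change is a within-patient test. Such a test can show that ARP fell after NCRT and that it fell after NCT. It gives neither an estimate nor a test of whether it fell further after one than after the other.

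The group tests do not clearly fill the gap. They are two-sample tests with no stated visit, scale or adjustment. Read in line with the sample-size basis, they compare ARP levels at follow-up. Because a team chooses the treatment for each patient, the groups may already differ in ARP at T1, for instance through tumour stage, age or sex. A comparison of levels would then credit that starting difference to treatment. At stake is the study's main conclusion: which part of the treatment harms the sphincter, and by how much.

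**Working it through.** **Inputs.** From Sample size: 122 per group before losses, SDs 17 and 18 mmHg, difference 45.3 − 32.7 = 12.6 mmHg. Pooled SD = √((17² + 18²)/2) = √306.5 = 17.51 mmHg. Alpha is 0.05, taken as two-sided because the sidedness is not stated. Assumed, because the article gives no figure: equal SD at both visits, and a correlation ρ between baseline and later ARP of 0.3 to 0.7.

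**The plan's own figure.** The 122 does not follow from these inputs. 2 × 306.5 × (1.960 + 0.842)² / 12.6² = 30.3, so 31 per group. That is a separate matter; 122 is used here only as the planned group size.

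**1. Comparing levels when true change is identical.** If two groups differ by d at T1 and change equally, they still differ by d at follow-up. Standard error of the difference = 17.51 × √(2/122) = 2.24 mmHg. The probability of significance is close to Φ(d/2.24 − 1.96).

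| Assumed baseline difference d (mmHg) | d/2.24 | Probability of p < 0.05 |
|---|---|---|
| 3 | 1.34 | about 27% |
| 5 | 2.23 | about 60% |

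The intended error rate is 5%.

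**2. What paired tests can say about differences.** SD of change = 17.51 × √(2(1 − ρ)), which is 17.51 at ρ = 0.5; its standard error is 17.51/√122 = 1.59 mmHg. Let every group have the same true change, and let p be the power of each paired test. Two groups give different verdicts with probability 2p(1 − p), and three are not unanimous with probability 1 − p³ − (1 − p)³.

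| True change, all groups (mmHg; ρ = 0.5) | p | Two groups disagree | Three not unanimous |
|---|---|---|---|
| 3 | 0.473 | 50% | 75% |
| 4 | 0.713 | 41% | 61% |
| 5 | 0.884 | about 20% | 31% |
| 12.6 | about 1 | about 0% | about 0% |

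At 3 mmHg, the figure for two groups is 46% at ρ = 0.3 and 43% at ρ = 0.7. For small changes, verdicts differ by chance alone. For large changes every test is significant, and the tests cannot rank the strategies.

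**3. Whether the planned size supports a comparison of change.** For 12.6 mmHg and 80% power, a change-score comparison needs 43, 31 or 19 per group at ρ = 0.3, 0.5 or 0.7. A baseline-adjusted comparison needs 28, 23 or 16. With 122 per group, power exceeds 99% in every case, and the difference in change detectable with 80% power is 7.4, 6.3 or 4.9 mmHg (change score) or 6.0, 5.4 or 4.5 mmHg (baseline-adjusted).

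**The case against.** The strongest reply is that between-group tests are planned. They stand in the sentence before the paired tests, the study is sized on a between-group difference, and a two-sample t test on change scores would answer the question. Nothing in the text rules that out. This stands, so it would be wrong to say the plan has only within-group tests. What remains is that change is mentioned only with the paired tests, and the one between-group comparison described in detail, in Sample size, is of levels.

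Three stronger readings are tempting, and the article does not support them.

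- **That a difference will be inferred from one significant and one non-significant paired test.** No such rule is stated. The disagreement rates show what paired tests cannot do; they do not forecast a false conclusion. They also depend on the assumed change and almost vanish at 12.6 mmHg.
- **That T2 goes unused, or that one before-and-after test in the NCRT group mixes neoadjuvant treatment with surgery.** The paired visits are not named, and T1–T2 and T2–T3 pairs fit the text.
- **That only a single longitudinal model will do.** A change-score or baseline-adjusted comparison at a fixed visit also answers the question.

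It can also be said that covariance structure and the handling of missed visits belong in a statistical analysis plan or full protocol. That is accepted, and their absence is not part of this point. The point is that the methods the article does fix do not match its aim.

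**Conclusion.** The point holds in a limited form. Statistical methods assigns within-patient tests to change and unadjusted two-sample tests, with no visit or scale, to groups. No stated analysis therefore compares change between the three strategies, although that is the aim and allocation is not randomised.

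If the group tests are applied to levels, a baseline imbalance of 3 or 5 mmHg alone gives a significant result in about 27% or 60% of studies. Those figures rest on 122 per group, an SD of 17.5 mmHg, identical true change and a two-sided 0.05 test. The size of the imbalance is assumed, and the article gives nothing from which to estimate it. If the group tests are applied to change, this problem goes away, which is why the choice should be stated.

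**What to change.** State the main analysis as a between-group comparison of change in ARP from T1 at a named visit, using baseline ARP and adjusting for age, sex and stage.

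- **One option** is a mixed model with T1 among the responses, group-by-visit terms and an unstructured covariance. A first-order autoregressive structure does not suit visits that follow treatment phases and then come every 3 to 6 months. Surgery-only patients have no neoadjuvant phase, so their T2 cell is left out by design.
- **An acceptable alternative** is a change-score or baseline-adjusted comparison at the named visit. Choose one beforehand, because they differ when baseline means differ: with identical change and a 3 mmHg baseline difference, the baseline-adjusted estimate is (1 − ρ) × 3 = 1.5 mmHg at ρ = 0.5, while the change-score estimate is 0.
- **Name the contrasts.** T1-to-T2 change in NCRT against NCT, for the added effect of radiotherapy, subject to confounding. Within-patient change across surgery, T2 to T3 after neoadjuvant treatment or T1 to T3 with surgery only. All groups have surgery, so its own effect rests on within-patient change; paired contrasts remain valid there and need not be reduced to description.

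The cost is wording, model assumptions to check and slightly more analysis work. Baseline ARP, age, sex and stage are already collected, and no extra patients or visits are needed. The text should be fixed before the data are analysed.

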#### Interventions

The eligible patients who voluntarily sign the consent form will undergo either NCRT with surgery, or NCT with surgery, or surgery only according to treatment guidelines. The protocol for neoadjuvant radiotherapy with conventional fractionation is as follows: 1.8-2.0 Gy per day per fraction from Monday to Friday for a total of 25 fractions and a total dose of 45–50 Gy during cycles 2–4 of neoadjuvant chemotherapy. The neoadjuvant chemotherapy scheme consisted of oxaliplatin 85 mg/m^2^ intravenously, leucovorin 400 mg/m^2^ intravenously, fluorouracil 400 mg/m^2^ intravenously, and fluorouracil 2.4 g/m^2^ for 48 h continuously intravenous infusion, to be repeated every 14 days for a total of 5–6 cycles. Surgery will be performed according to the standard total mesorectal excision principles.

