### Sample size

The sample size calculation was performed considering the results of a previous case-control study with rectal cancer patients undergoing chemoradiotherapy and/or surgery [25]. In this study, RP was significantly lower in the chemoradiotherapy group than in the surgery group (32.7 +/- 17 vs. 45.3 +/- 18 mmHg; P = 0.03) at the time of ileostomy closure. These values were introduced at PASS v11 software (NCSS, LLC. Kaysville, Utah, USA) with a power of 80%, alpha 0.05, and an enrollment ratio of 1/1, resulting in an estimated sample size of 122 participants in each group. Then, considering the need of lost to follow-up, which is estimated at around 10.0% of the cases, a total of 134 patients in each group will be required in this study.

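### An unadjusted 5% threshold for every test, with no declared contrast or visit for the primary outcome, materially inflates the primary type I error

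*Protocol article*

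**What the plan says.** Outcomes section: "The primary outcome is the average resting pressure (ARP) of anal sphincter". No visit, no change-from-baseline definition and no group contrast is attached to it. The same section schedules assessments at T1 (baseline), T2 (after neoadjuvant treatment), T3 (after surgery, before stoma closure) and then every 3 to 6 months, with at least 2 years of follow-up.

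Interventions section: patients receive "either NCRT with surgery, or NCT with surgery, or surgery only according to treatment guidelines", so there are three groups and three pairwise contrasts.

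Statistical methods section: continuous outcomes are compared between groups by t or Mann-Whitney tests, and before/after values by paired t or Wilcoxon tests. Categorical variables get chi-square or Fisher tests. On the threshold: "A significance threshold of p < 0.05 will be adopted for all tests".

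Sample size section: the only place where one comparison at one time appears. It cites a previous study in which "RP was significantly lower in the chemoradiotherapy group than in the surgery group", with the values "32.7 +/- 17 vs. 45.3 +/- 18 mmHg; P = 0.03) at the time of ileostomy closure". Neither the Outcomes nor the Statistical methods section takes up that comparison.

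**The concern.** The study is sized for one two-group comparison at one time, but the analysis section gives that comparison no special standing. Read as written, every between-group test of resting pressure, at any visit and for any pair of groups, is judged at the same 5% level, and each could be presented as the primary result. The 5% error rate then holds for each test separately, not for the primary question.

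The study aims to inform treatment strategy. One nominally significant difference at a single late visit could be reported as evidence that a regimen harms sphincter function, and a reader could not tell the planned comparison from a selected one.

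**Working it through.** **Inputs from the article.** Three groups; a per-test threshold of 0.05; visits T2, T3 and then every 3 to 6 months for at least 2 years; means 32.7 (SD 17) and 45.3 (SD 18) mmHg; 122 per group before and 134 after allowance for loss.

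**Assumptions (not in the article).** The 2 years run from T3, so there are 24/6 = 4 to 24/3 = 8 follow-up visits. Surgery-only patients have no post-treatment T2. Within-patient correlation between visits is 0.4 to 0.8, equal for every pair of visits. Tests are two-sided. There are no true group differences at any visit.

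**1. The plan's own sample size.** The article reports "with a power of 80%, alpha 0.05, and an enrollment ratio of 1/1, resulting in an estimated sample size of 122 participants in each group".
- Pooled SD = √((17² + 18²)/2) = √306.5 = 17.51; difference = 45.3 − 32.7 = 12.6.
- n per group = 2 × (1.960 + 0.842)² × 306.5 / 12.6² = 30.3, so 31 (32 by the exact t test).
- The stated 122 is not reproduced. It appears if the difference is halved: 2 × (1.960 + 0.842)² × 306.5 / 6.3² = 121.2, so 122.
- Loss allowance: 122 × 1.1 = 134.2, and 3 × 134 = 402, which agrees with the stated total.

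The gap between 31 and 122 is a separate matter. It is noted here because it affects what a multiplicity correction would cost (step 5).

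**2. Number of between-group tests of resting pressure.**
- T2: 1 test (chemoradiotherapy vs chemotherapy).
- T3 and each follow-up visit: 3 tests.
- Total = 1 + 3 × (1 + 4) = 16, up to 1 + 3 × (1 + 8) = 28.

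**3. Chance of at least one p < 0.05 at a single visit.** Three independent tests would give 1 − 0.95³ = 14.3%. Each pair of contrasts shares a group, and simulation of the three pairwise tests gives 12.2%.

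**4. The same chance over all visits.** Independent tests would give 1 − 0.95¹⁶ = 56% and 1 − 0.95²⁸ = 76%. Allowing for shared groups and correlated visits (200,000 simulated studies per cell):

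| Follow-up visits (tests) | correlation 0.4 | 0.6 | 0.8 |
|---|---|---|---|
| 4 (16) | 44% | 38% | 29% |
| 8 (28) | 60% | 49% | 36% |

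Widening the correlation to 0 to 0.9 gives 51% down to 24% for 16 tests and 71% down to 28% for 28 tests. Within-group paired tests and the three secondary outcomes are not counted.

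**5. Effect of the remedies.**
- One declared contrast at one visit: primary type I error 5%, and power for that contrast unchanged.
- Global three-group test at one visit, then pairwise tests at 0.05 only if it is significant: simulated family error 5.0%.
- Bonferroni at 0.05/3 with 122 per group: power above 99.9% if the difference is 12.6 mmHg, but about 66% (against 80% for one test at 0.05) if 122 really rests on 6.3 mmHg.

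**The case against.** - **Detail left elsewhere.** Visit hierarchy and multiplicity procedures are often left to an analysis plan, and the Statistical methods section is a condensed paragraph. That would excuse silence. It does not excuse a stated rule that every test uses 0.05, because a later plan that adjusted for multiplicity would contradict it.
- **An intended comparison is visible.** The Sample size section points to chemoradiotherapy versus surgery "at the time of ileostomy closure". This stands as evidence of intent and makes the fix easy, but nothing declares that comparison primary.
- **A false-positive primary finding is likely.** A reader might infer this, but the article does not support it. The probability stays below one half in every 16-test scenario at correlations of 0.4 to 0.8, and passes it only with many visits or low correlation. All the figures also assume no true differences, whereas the article cites evidence that treatment does affect function.
- **Any one significant test counts as success.** The article does not say so. It only fails to rule it out.
- **Observational design.** Treatment is chosen by a multidisciplinary team, so a group difference may reflect selection even if only one test is run, and strict family-error control in such a study is debated. This stands and lowers the severity. It does not remove the need to say which comparison is primary.

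**Conclusion.** The point holds as a material inflation of the primary type I error. It is about 12% instead of 5% at a single visit with three pairwise tests. It is roughly 30% to 60% over 16 to 28 between-group tests, given no true differences, a within-patient correlation of 0.4 to 0.8 and 4 to 8 follow-up visits after T3. The visit count is derived from the schedule and the correlation is assumed, so the exact figure is uncertain. No scenario examined with more than one contrast or visit brings the error back to 5%. This should be fixed. It is not a fatal flaw, given the observational design and a sample size that already implies one comparison.

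**What to change.** In the Outcomes and Statistical methods sections, declare one primary analysis: average resting pressure at T3, chemoradiotherapy with surgery versus surgery only, tested at two-sided 0.05. This is the comparison closest to the one behind the sample size. Replace the sentence on the threshold for all tests with a statement that every other contrast, visit and outcome is secondary or exploratory and is reported with confidence intervals.

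If the investigators mean all three contrasts at T3 to be primary, they should instead run a global three-group test at 0.05 and make the pairwise tests at 0.05 only if it is significant. With exactly three groups this holds the family error at 5%. One scheme should be chosen, not both: a single pre-specified contrast needs no global test in front of it.

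The cost is a few sentences and a lower standing for the other comparisons. Under the single-contrast scheme no power is lost for the declared comparison and no more patients are needed. Either scheme should be fixed before results are examined.
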